**Confirmatory Observation**		
Visual or tactile identification of a local twitch response	X	X
Pain or altered sensitivity (in the predictable distribution of an MTrP in that muscle) upon compression of the tender nodule	X	X

MTrPs: myofascial trigger points.

The Spanish versions of FSFI, PFDI-20, and PFIQ-7 questionnaires, and the Broome scale are self-administered. Participants will complete them independently online through Google Forms, which will be sent to their email addresses immediately after each physiotherapy assessment.

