#### 2.2.2. Sample Size

The sample size was calculated based on the results obtained by Citak et al. [35], using the Female Sexual Function Index (FSFI) scores as a reference and the statistical program GRANMO 8.0 (Datarus, Barcelona, Spain). Assuming a two-tailed test with an alpha risk of 0.05 and a statistical power greater than 0.8, 62 participants per group will be required to detect a difference of 2.4 points or greater. A common standard deviation of 4.5 was assumed. Additionally, a 10% dropout rate was accounted for in the estimation.

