#### 2.2.3. Physiotherapy Assessments

Physiotherapy assessments will be conducted by a physiotherapist specializing in Pelvic and Women’s Health (PT1) with over 10 years of experience, who will be blinded to the participants’ intervention group. The physiotherapy assessment will include an interview to collect socio-demographic and clinical history data, as well as a physical examination (Table 1). The outcome variables of the study that will be collected at all assessments are as follows:Primary outcomes:
(1)Pelvic pain: The perceived pain intensity will be measured using the Visual Analog Scale (VAS). This scale consists of a 100 mm horizontal line, where the participant marks the intensity of their pain, with the left margin of the line representing “no pain” and the right margin representing “the worst possible pain.” A minimum detectable change (MDC) of 15 mm is required for clinical significance [36].(2)Female sexual function: The Spanish version of the FSFI will be used [37]. The FSFI questionnaire has a scoring range from 2 to 36 points, with higher scores indicating better sexual function. It assesses six domains: desire, arousal, lubrication, orgasm, satisfaction, and pain. A change of 6 points will be considered clinically relevant [38].Secondary outcomes:

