
**Table 1 jcm-14-01489-t001:** Study assessed variables and evaluations.

Assessed Variables	Assessment				
	A0	A1	A2	A3	A4
Sociodemographic variables (address, telephone number, mail, profession, studies, date of birth)	X	only if changes	only if changes	only if changes	only if changes
General clinical data (weight, height, medication, diagnosed pathologies, surgeries, allergies, sports routines, healthy habits)	X	only if changes	only if changes	only if changes	only if changes
Gynecological history (pregnancies, weight gain during pregnancy, type of delivery, presence and degree of tear, presence of episiotomy, weight and length of the baby, breastfeeding, menstruation, symptoms of pelvic floor dysfunction)	X	only if changes	only if changes	only if changes	only if changes
Pelvic floor observation (contraction capacity, relaxation capacity, apnea, parasitic muscle contraction, reflexes, symmetries, perineal scars)	X	X	X	X	X
PFM objective evaluation (Modified Oxford scale, tone and strength by vaginal dynamometry; rest, PFM contraction and bearing down by transperineal ultrasound)	X	X	X	X	X
Diagnosis of MPS (pain: description, intensity, body chart, triggering factor; palpation of abdominal and pelvic floor surface and deep muscles)	X	X	X	X	X
Questionnaires (FSFI, PFDI-20, PFIQ-7, Broome scale)	X	X	X	X	X

A0: pre-treatment assessment, A1: post-treatment assessment, A2: 3-month assessment after treatment, A3: 6-month assessment after treatment, A4: 12-month assessment after treatment, PFM: pelvic floor muscles, MPS: myofascial pain syndrome, FSFI: Female Sexual Function Index, PFDI-20: Pelvic Floor Distress Inventory–short form, PFIQ-7: Pelvic Floor Impact Questionnaire–short form.

**Table 2 jcm-14-01489-t002:** Diagnostic clinical criteria for identifying active and latent myofascial trigger points.

Essential Criteria	Active MTrPs	Latent MTrPs
Palpable taut band	X	X
Exquisite local tenderness upon pressure over a nodule within the taut band	X	X
Patient recognition of their typical pain upon pressure applied to the tender nodule	X	
Painful limitation of the range of motion upon full muscle stretch	X	X

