#### 2.2.4. Follow-Up

Assessments will be conducted at four time points by the same blinded physiotherapist (PT1): before the intervention (A0), after the physiotherapy intervention (A1), and at three follow-ups, 3-, 6- and 12- months post-treatment (A2, A3, and A4, respectively).

The assessment appointment will be scheduled with them, and a reminder will be sent via SMS and email. If they are unable to attend, they will have access to a phone number and email address to contact, and another appointment will be scheduled with them.

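### Emailing of the online questionnaires is tied to the in-person examination, so a missed visit delays the FSFI and may lose it, although the form needs no visit

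*Protocol article*

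**What the plan says.** Section 2.2.3 lists the FSFI as the second primary outcome, and section 2.2.2 bases the sample size on it, "using the Female Sexual Function Index (FSFI) scores as a reference". The FSFI, PFDI-20, PFIQ-7 and Broome scale are self-administered: "Participants will complete them independently online through Google Forms", by forms "which will be sent to their email addresses immediately after each physiotherapy assessment".

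Table 1 schedules these questionnaires at A0 to A4. At the same five assessments it schedules palpation of the pelvic floor and an objective muscle evaluation that covers "tone and strength by vaginal dynamometry; rest, PFM contraction and bearing down by transperineal ultrasound".

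Section 2.2.4 provides for an SMS and email reminder of the appointment. For a woman who cannot come, there is a telephone number and an email address, and "another appointment will be scheduled with them".

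On attrition, section 2.2.2 says: "Additionally, a 10% dropout rate was accounted for in the estimation".

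**The concern.** An outcome that can be collected by email from anywhere is given a trigger that depends on an intimate on-site examination. The only stated response to non-attendance is another such appointment, so the FSFI moves with the visit. A woman rebooked some weeks late answers the FSFI at the rebooked date and not at the nominal 3, 6 or 12 months. For a woman who declines the examination or never returns, no route to the FSFI is described.

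Two things are at stake. One is precision, because the FSFI is the outcome on which the trial is sized. The other is bias. Women know their allocation (section 2.1), and the palpation tests whether pressure reproduces their usual pain (Table 2). Willingness to come back for it may therefore depend on pain, on sexual function and on how a woman views the treatment she received. The plan itself recognises attendance as an issue: question 4 of the interview guide (Table 3) asks whether it was easy or difficult to attend the treatment and evaluation sessions.

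**Working it through.** **The stated rules, followed in order.**

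1. Visit attended on time: the form goes out that day and the FSFI is on schedule.
2. Visit missed and rebooked: the form goes out after the rebooked visit, and the FSFI is late by the same interval.
3. Visit never attended: the stated trigger does not occur. The article does not say whether the form is sent anyway.

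Case 2 follows from the text. Case 3 is a possible loss, not a stated one.

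**Inputs (section 2.2.2).** FSFI difference δ = 2.4; common SD σ = 4.5; two-sided alpha 0.05; power above 0.8; 10% dropout; 62 per group.

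**The plan's own figure.** The number evaluable per group is

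n = 2 × [σ(1.960 + 0.842)/δ]² = 2 × [4.5 × 2.802/2.4]² ≈ 55.2, rounded up to 56.

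With 10% dropout, 55.2/0.9 = 61.3, rounded up to 62 (56/0.9 = 62.2, rounded up to 63). The stated 62 per group is reproduced.

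**Sensitivity to missing FSFI.** With a proportion d missing in each arm, m = 62(1 − d), and by the normal approximation

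power = Φ(δ / [σ√(2/m)] − 1.960).

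For d = 0.10, m = 55.8, the standard error is 4.5 × √(2/55.8) = 0.852, 2.4/0.852 = 2.817, and Φ(0.857) = 0.804. The other rows follow in the same way. The t-test column uses the same inputs.

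| FSFI missing per arm | m | Power, normal | Power, t-test |
|---|---|---|---|
| 0% | 62.0 | 0.844 | 0.838 |
| 10% (planned) | 55.8 | 0.804 | 0.797 |
| 15% (assumed) | 52.7 | 0.782 | 0.774 |
| 20% (assumed) | 49.6 | 0.757 | 0.748 |

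To hold 80% power, the number randomised per group would have to be 56/0.85 = 65.9, so 66, at 15% loss, and 56/0.80 = 70 at 20% loss.

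These figures describe a single between-group comparison at one time point, without baseline adjustment, as in the plan's own calculation. They show how little room the 10% leaves. They do not measure what the email trigger costs, because the documents give neither a non-attendance rate nor a rate at which non-attenders would answer an emailed form.

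**The case against.** The sentence on emailing can be read as a description of the usual workflow. It gives a time and does not state an exclusive condition, and Table 1 shows the questionnaires as a row of their own, due at every time point. A reader might infer that the forms go only to women who attend, so that every missed visit loses the primary outcome. The documents do not support that. They do not say that forms are withheld from non-attenders, and reminders and rebooking mean that a missed visit first produces a delay. Loss requires both that the woman never comes and that staff do not send the form anyway. Nor does the text say that women who stop treatment leave the assessments.

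It can also be said that a journal article leaves the handling of persistent non-attenders to the full protocol. That is fair for visit windows and similar detail. It does not dispose of the point, because the article does state a trigger, and a better one is available at almost no cost.

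Three further objections stand. The power range is generic attrition, and its 10% row is the plan's allowance working as intended. That the loss would be informative is plausible but not documented. Finally, VAS pain, the other primary outcome, appears in Table 1 within the in-person assessment (as pain intensity, under the diagnosis of MPS), so changing the trigger for the forms leaves it as dependent on attendance as before.

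**Conclusion.** The point holds as a cheap improvement to a stated procedure. It is not an error in any figure: the sample size is reproduced. As written, collection of the FSFI depends on the physical visit. A missed visit delays it, and a visit that never happens may lose it, for a form that needs no visit.

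The size of the extra loss is unknown. On assumed losses of 15% and 20% in place of the planned 10%, power falls from about 0.80 to about 0.78 and 0.75 to 0.76. This assumes equal loss in both arms and the plan's difference and SD, and it leaves out any bias from who is missing. A reader might take the fall in power as the cost of the email trigger. It is not: the documents link no share of attrition to that trigger.

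**What to change.** In section 2.2.3, state that for A1 to A4 the questionnaire link is sent to every randomised woman on the due date of the assessment, whether or not she attends and whether or not she completed treatment. Extend the existing SMS and email reminders to the forms, and record the date on which each form is completed.

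The cost is a sentence or two in the protocol and a change to when an existing link is sent. No new staff, instrument or visit is needed. The downside is that some FSFI scores will have no matching physical measures, or none from the same day. VAS pain would still be collected only at the visit, and the text should acknowledge this.

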#### 2.2.4. Follow-Up

Assessments will be conducted at four time points by the same blinded physiotherapist (PT1): before the intervention (A0), after the physiotherapy intervention (A1), and at three follow-ups, 3-, 6- and 12- months post-treatment (A2, A3, and A4, respectively).

The assessment appointment will be scheduled with them, and a reminder will be sent via SMS and email. If they are unable to attend, they will have access to a phone number and email address to contact, and another appointment will be scheduled with them.

#### 2.2.5. Intervention

Participants will be randomly assigned in a 1:1 ratio to one of two intervention groups using a computer-generated randomization sequence (Epidat 4.2, Xunta de Galicia, Spain). To ensure allocation concealment, the randomization sequence will be generated in advance by an independent researcher and stored in sealed, opaque, consecutively numbered envelopes. These envelopes will be securely kept and opened only by the designated physiotherapist (PT2) at the time of each participant’s enrollment. PT2 will not be involved in participant assessment or treatment to prevent potential allocation bias. Block randomization with variable block sizes will be used to maintain balance between groups throughout the study.

Participants will be allocated to either the active control group receiving multimodal physiotherapy (MP-G) or the experimental group receiving multimodal physiotherapy including radiofrequency (RMP-G). Both interventions will be individualized and administered by physiotherapists specializing in Pelvic and Women’s Health (PT3 and PT4), who will remain blinded to group allocation to ensure assessor masking. The approximate session duration will be 45 min per session, twice a week for 6 weeks, totaling 12 sessions. Both groups will receive therapeutic education, specific PFMT, and conservative and/or invasive treatment for MPS, with the addition of radiofrequency in the RMP-G. The details of each treatment strategy are explained below.

Therapeutic education (MP-G and RMP-G): Learning about the anatomy, physiology, and pathophysiology of the abdominopelvic cavity, pelvic floor dysfunctions, and risk factors through anatomical slides and audiovisual resources. This also includes the concept of pain and its associated factors, as well as individual strategies to manage pain and improve and/or protect the pelvic floor.PFMT (MP-G and RMP-G): Active, specific PFM exercises, guided intravaginally with one or two contacts by the physiotherapist. These exercises involve different types of contractions aimed at improving proprioception, strength, endurance, and relaxation capacity. Participants will be encouraged to perform PFMT at home at least twice a week, as well as to include the knack maneuver during perceived increases in intraabdominal pressure.Conservative and Invasive Treatment of MPS (MP-G and RMP-G): After diagnosing MPS, active MTrPs will be treated through conservative techniques: dynamic and static compression of the MTrPs, local longitudinal massage of the muscle taut band, fascial massage of adjacent muscles, and local stretching of muscle fibers. If, after two sessions, the pain of the active MTrPs does not improve, dry needling will be used. Latent MTrPs will be treated with conservative techniques [39].Non-ablative radiofrequency (RMP-G): The treatment will begin in the third session, using capacitive superficial electrodes (Ø35 mm) (which penetrate less deeply into the tissue) and resistive superficial (Ø30 mm) and intravaginal (longitudinal, Ø14 mm) electrodes (for deeper tissues). A capacitive electrode protocol will be applied for 5–10 min using circular movements over the scar region (if present), the perineal body, and the labia majora with a bio-stimulation effect and a participant’s perception of heat of 0–2 on a 10-point scale for 2–3 min; and with a vascularization effect and a participant’s perception of heat of 6–7 on a 10-point scale for 2 min. This will be followed using a resistive external and intravaginal electrode, which promotes vascularization of the PFM, with a heat sensation of 6–7 on a 10-point scale for 15–20 min. The external resistive electrode will be applied in circular motions over the same areas as the external capacitive electrode, as well as the suprapubic region, while combining this with PFMT and conservative treatment for MPS. The intracavitary resistive electrode will perform a “U” movement along the vaginal fornix, pausing at areas with muscle taut bands and combining this with PFMT. The session will conclude with the application of a capacitive surface electrode for 5 min on the scar tissue and perineal body, with a subjective heat sensation of 0–2 on a 10-point scale. A radiofrequency device INDIBA^TM^ ACTIV 7 (Indiba S.A, Barcelona, Spain) will be used. This device operates at a fixed frequency of 448 kHz, with a maximum power of 250 VA in capacitive mode and a maximum power of 130 W in resistive mode. The intensity will be set based on the patient’s subjective perception, ranging from 0 to 2 for bio-stimulation effects, and 6 to 7 for a heating sensation to achieve a vascularizing effect.

To assess the safety of the interventions, in all treatment sessions, the physiotherapists performing the treatments (PT3 and PT4) will record any potential incidents, such as discomfort, increased pain, use of medication, need for additional medical consultations, postponement, or suspension of treatment due to possible adverse effects of the interventions.

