## 2. Materials and Methods

### 2.1. Study Design

The RASDOP study is a mixed-methods study comprising a single-blind RCT and a qualitative component. The RCT will follow a two-parallel-arm design. Outcome assessment will be blinded, meaning that the evaluators conducting the assessments will not be aware of the participants’ group allocation to reduce detection bias. However, due to the nature of the interventions, neither participants nor treating physiotherapists will be blinded. In parallel, a qualitative study will be conducted using a phenomenological approach, involving individual and group interviews with women from the RCT.

This study has been approved by the Research and Animal Experimentation Ethics Committee of the University of Alcalá under registration number CEIP/2023/3/056. This study has also been registered on the ClinicalTrials.gov platform under the identification code NCT06469632.

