(1)Myofascial pain syndrome (MPS): The presence of MPS will be identified by assessing myofascial trigger points (MTrPs) in the abdominal muscles and PFM. To diagnose MPS, at least one active MTrP must be identified. The essential clinical criteria proposed by Travell and Simons will be followed (Table 2) [39]. Additionally, confirmatory observations will be recorded, such as the presence of referred pain elicited by palpating the MTrP [40].(2)Pelvic floor dysfunction perceived distress: Evaluated using the transculturally validated Spanish version of the Pelvic Floor Distress Inventory–short form (PFDI-20) [41]. The PFDI-20 is scored from 0 to 300, with higher scores indicating greater distress caused by pelvic floor dysfunctions. It assesses lower urinary tract symptoms, anorectal symptoms, and pelvic organ prolapse symptoms. A minimal important change of 23% will be considered clinically significant [42].(3)Impact of pelvic floor dysfunctions: Assessed using the Spanish version of the Pelvic Floor Impact Questionnaire–short form (PFIQ-7) [41], which includes three subscales related to urinary, intestinal, and prolapse symptoms. Each subscale is scored from 0 to 100, where a higher score indicates a greater impact and worse quality of life. An MDC of 16% is required for clinical significance [43].(4)Pelvic floor muscles tone: PFM tone will be assessed using vaginal dynamometry (Pelvimetre™, Phenix Vivaltis, Montpellier, France). The participant will be in the lithotomy position, and the lowest value automatically recorded by the device will be taken after instructing the woman to relax her PFM. A MDC of 5 g will be considered [44].(5)Pelvic floor muscle strength: PFM strength will be measured in the lithotomy position by requesting three maximal PFM contractions. The average value of the three contractions will be considered. A vaginal dynamometer (Pelvimetre™, Phenix Vivaltis, Montpellier, France) will be used for the measurement, and a MDC of 50 g will be considered [44].(6)Levator hiatus length: Using 2D transperineal ultrasound (Mindray M7, Shenzhen, China) in the sagittal plane, the distance between the inferior margin of the pubic symphysis and the anorectal angle will be assessed [45]. Measurements will be taken at rest, during maximal PFM contraction, and during a strain effort.(7)Perceived self-efficacy: assessed using the Broome Pelvic Muscle Self-Efficacy Scale–Spanish version [46]. This scale evaluates expectations of self-efficacy in performing specific PFM exercises and expectations regarding the anticipated outcomes. The maximum score is 100 points, indicating high self-efficacy, while a score below 33 points indicates low self-efficacy [46].

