## 4. Discussion

To the authors’ knowledge, this is the first RCT with evaluator blinding to compare the effectiveness of a multimodal physiotherapy treatment versus a multimodal treatment that includes non-ablative radiofrequency in managing pelvic pain and sexual function from six weeks to six months postpartum. The significance of the RASDOP study lies in addressing the fact that nearly 50% of women develop symptoms of pelvic pain and/or dyspareunia following childbirth [12,13]. If left untreated, this pain can persist over time [49], negatively impacting sexual function, mental health [50], quality of life, and even the desire to have more children.

Previous studies have evaluated the efficacy of radiofrequency in pelvic pain immediately after childbirth [51,52]. These include two double-blind RCTs comparing the immediate use of radiofrequency versus placebo in women following vaginal delivery. Two consecutive sessions were conducted during the participants’ hospital stay, and perineal pain was assessed at rest, while sitting, and during walking. Bretelle et al. [51] reported improvements in walking pain and reduced analgesic consumption in the study group. In contrast, Sierenska et al. [52] found that radiofrequency improved pain and discomfort at rest, while sitting, and while walking but did not observe a reduction in the consumption of paracetamol or ibuprofen. In the acute phase, perineal trauma can be the primary source of pain, which may sometimes improve with medication or local cooling [53]. However, this pain can persist over time, potentially involving other structures, such as the PFM, as the primary source of discomfort. The RASDOP study proposes applying radiofrequency not only to scars but also to the PFM and abdominal muscles, aiming to improve the MTrPs in these muscles. Radiofrequency has only demonstrated short-term effects, and existing studies have heterogeneous protocols, small sample sizes, or lack a control group [28]. Therefore, more evidence is needed to support the use of radiofrequency for pelvic pain, as well as the additional financial cost associated with this technology. Additionally, radiofrequency is a passive treatment technique, while maintaining long-term benefits requires behavioral modifications and the adoption of active treatment strategies [54]. Therefore, the RASDOP study will include educational management and PFMT in both treatment groups.

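### Section 2.2.5 says the treating physiotherapists stay blinded to allocation, which contradicts section 2.1 and is impossible once they deliver radiofrequency

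*Protocol article*

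**What the plan says.** Section 2.1 (Study Design) describes a single-blind trial in which the evaluators do not know the allocation. It adds that "due to the nature of the interventions, neither participants nor treating physiotherapists will be blinded". Sections 2.2.3 and 2.2.4 name PT1 as the blinded physiotherapist who carries out the assessments.

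Section 2.2.5 (Intervention) has PT3 and PT4 deliver both interventions and describes them as physiotherapists "who will remain blinded to group allocation to ensure assessor masking". It also says that the allocation envelopes are "opened only by the designated physiotherapist (PT2) at the time of each participant’s enrollment", and that PT2 takes no part in assessment or treatment.

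The same section gives both arms education, pelvic floor muscle training and treatment of myofascial pain, with this escalation rule: "If, after two sessions, the pain of the active MTrPs does not improve, dry needling will be used". Radiofrequency belongs to the experimental arm only, and "The treatment will begin in the third session" of 12. On safety, "the physiotherapists performing the treatments (PT3 and PT4) will record any potential incidents".

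**The concern.** The two sections make opposite statements about the same people. The one in section 2.2.5 describes a property that the design cannot have. A therapist who moves a radiofrequency electrode over or inside the patient knows that she is in the radiofrequency arm.

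Two things that PT3 and PT4 do depend on how their masking is described. The first is the incident record, which is the trial's stated means of assessing safety. The second is the step up to dry needling, which follows from a judgement that pain has not improved, and the article gives no threshold for that judgement. Needling treats the active trigger points on which a secondary outcome rests: "To diagnose MPS, at least one active MTrP must be identified". Section 4 says that radiofrequency is applied to the pelvic floor and abdominal muscles "aiming to improve the MTrPs in these muscles", so knowing that it is coming, or being given, could plausibly influence whether a therapist needles. If it did, the arms would differ by more than the added radiofrequency. A reader who trusts section 2.2.5 would rule this out on grounds that do not exist.

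**Working it through.** No stated figure bears on this point, and it does not depend on the sample size. The check sets the statements side by side and puts the events in order.

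1. **Who is masked.** Section 2.1: treating physiotherapists are not. Section 2.2.5: PT3 and PT4, who are the treating physiotherapists, are. The two statements conflict directly.

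2. **Which statement can be true.** Radiofrequency starts in session 3 and is delivered by PT3 and PT4. From then on they see which arm each patient is in, so section 2.2.5 is false for those sessions. Its stated purpose, masking the assessor, does not fit them either, because the assessor is PT1. Section 2.1 is therefore the workable statement for the course as a whole.

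3. **How much of the course is affected.** Total sessions: 12 (section 2.2.5). Same content in both arms: sessions 1 and 2, so 2/12 = 17%. Different content: sessions 3 to 12, so 10/12 = 83%. These are counts of sessions and do not measure bias.

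4. **Order of events.** The envelope is opened at enrollment by PT2. Sessions 1 and 2 follow, with the same content in both arms. A needling decision can fall due after session 2. Radiofrequency starts in session 3. A decision taken between sessions 2 and 3 therefore comes after the envelope is opened but before the arms differ in content.

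5. **What is and is not known at that moment.** The article does not say when PT3, PT4 or the participant learn the arm. They may know it when the first needling decision is made, or they may not. The reason section 2.1 gives for not blinding, the nature of the interventions, has no force in sessions 1 and 2.

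6. **Later needling decisions.** The rule can also be read as two sessions of treating a given trigger point. Conservative treatment of myofascial pain continues alongside radiofrequency, so further decisions may arise after session 3. Those cannot be masked from the therapist.

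**The case against.** The strongest reply is that this is a misplaced clause. Section 2.1 is explicit and gives a reason, section 2.2.5 names assessor masking as its aim, and PT1's masking is unaffected. That is probably how the sentence arose, and it limits the consequence. It does not make the sentence right. As printed, section 2.2.5 claims therapist masking that the trial does not have.

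A reader might go further and infer that the first needling decision is taken with knowledge of the arm and that this biases the comparison. The documents do not support that:

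- They do not say when PT3 and PT4 are told, and a journal article commonly leaves such operational detail to the full protocol.
- The needling rule is identical in both arms.
- They give no needling rate and no needling benefit. The direction is unknown and zero is possible.
- The outcome most directly tied to needling, myofascial pain syndrome, is secondary. No effect on the primary outcomes, VAS pain and FSFI, is shown.
- The comparison of the two strategies as delivered stays valid even if needling differs between arms.

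A reader might also infer that the rule is applied once, after session 2, so that all needling could be decided masked. The text does not fix that reading. Limiting needling to a single decision would change a treatment that the protocol describes as individualized. That part of the objection stands, and the suggestion below leaves later needling open.

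**Conclusion.** The statement in section 2.2.5 that PT3 and PT4 remain blinded is wrong as written. It contradicts section 2.1 and cannot hold from session 3, which is 10 of the 12 sessions. What follows is a limit on what the trial may claim: needling decisions and the incident record kept by PT3 and PT4 should not be presented as masked. The conclusion rests only on PT3 and PT4 delivering the radiofrequency, which the section states. No bias is quantified or asserted in either direction, and the masking of outcome assessment by PT1 is not in question. This is a low-severity point that merits correction because the correction costs almost nothing.

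Delaying disclosure of the arm until session 3 is a secondary suggestion. It is feasible because the first two sessions have the same content in both arms and PT2, who opens the envelope, neither treats nor assesses.

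**What to change.** **Correction.** In section 2.2.5, replace the clause on PT3 and PT4 with a statement that PT1 is masked throughout and that PT3 and PT4 are not masked, at the latest from session 3. Describe needling decisions and the incident record accordingly. Cost: one sentence.

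**Optional improvement.** Have PT2 withhold the allocation from PT3, PT4 and the participant until session 3. The participant is included because the rule depends on her reported pain, and section 2.1 now says without qualification that she is not blinded. Record any needling decision due after session 2 before disclosure. Later needling decisions stay allowed and are acknowledged as unmasked. Report the number of women needled by arm, descriptively.

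Cost: one added sentence, one line on the treatment record, one table row and one delayed hand-over by PT2, whose described role now ends at enrollment. Section 2.1 would need a matching qualification for the first two sessions. No extra visit, session time or sample size is needed. If enrollment has begun, the correction and the count by arm are still possible for everyone, and delayed disclosure can apply to later participants.
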